### Sample size and duration of the study

The sample size has been calculated for the primary outcome (death or liver decompensation) with 80% power and 5% risk of type I error. We anticipate that 5% of all included patients (treated and untreated) will either die or experience liver decompensation within 3 years, with the standard model [20], and we want to detect a 50% relative reduction (Odds Ratio of 0.5 or less) with the test-and-treat model. This results in a sample size of 997 patients per arm [21]. We will increase the sample size by 50% and aim for 1,500 patients per model of care arm, due to expected attrition. This results in a total of 4,500 patients at six different sites. Assuming that approximately 9% of those living in the study setting are hepatitis B surface antigen (HBsAg) positive and 50% of those screened can be included in the study, we estimate that we need to screen approximately 100,000 individuals in order to enroll 4,500 CHB patients.

As inclusion rates may vary across sites, we plan to continue inclusion until all models of care have reached 1500 inclusions, accepting an uneven distribution between the two clinics assigned to the model. We expect to complete inclusion within 1 year. As the observation period will be three years, the total study period will be four years. The first participant was enrolled at September 5, 2024, and recruitment is ongoing. 

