### Statistical analysis 

Results will be reported using descriptive statistics. Continous data will be reported as mean with standard deviation (SD), and categorical data as number with percentage. Cox proportional hazards regression models will be used to analyze the primary outcome (death and liver decompensation). The primary purpose of the analysis is to assess the association between the model of care and time to event, accounting for potential confounding factors. We will estimate hazard rations (HR), and 95% confidence intervals (CI) for the association between care model type (standard, simplified, test-and-treat) and the outcome. The model will be adjusted for baseline covariates known to be associated with adverse outcome, including age, sex and liver cirrhosis. The proportional hazards assumption will be tested using Schonefeld residuals. Individuals lost to follow-up will be right-censored at the last data known to be alive. Unadjusted survival functions will be estimated using Kaplan-Meier methods and compared using the log-rank test. A sensitivity analysis assuming that all individuals with missing outcome data at the end of the observation period reached the primary outcome (worst case scenario) will be performed.

In a secondary analysis, we will compare outcome variables in the decentralized models with previous results from a centralized model [4]. This comparison will have its inherent limitations due to differences in demography, co-morbidity, and available resources, which we can only partly adjust for in statistical models. However, it will still be of value to be able to assess the decentralized models in a wider context.

STATA (College Station, TX, USA) and/or R Core Team (2024) will be used to analyze the data.

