## Discussion

Here, we provide the structure and details of a prospective, multicenter cohort study assessing decentralized hepatitis B care in Ethiopia, aiming to compare three distinct models of care. We will assess clinical and programmatic outcomes over a 3-year period, and utilize methods from implementation science to assess the context where CHB treatment and care will be implemented. The study may have implications for patients with CHB as well as national and international health authorities and stakeholders, as the number of deaths due to CHB in the WHO Africa region is increasing and countries in the same region are struggling to make progress in their hepatitis B elimination efforts [1]. If one of the models is found to be superior and more and feasible to implement, it could be considered for broader implementation in other countries in the region.

One strength of the study is the utilization of existing health infrastructure, as we believe this increases sustainability and transferability of the study results. Besides training of staff, the study will utilize existing health structures and staff employed at local clinics/hospitals, to strengthen regional health authorities and ensure local support. Generalizability is increased by having two sites from separate regions of Ethiopia in every treatment model, and by taking a«real-world» pragmatic approach by having broad inclusion criteria and limited exclusion criteria. Key challenges will be to ensure that the six sites are able to complete the necessary screening efforts and reach the predefined sample size. Furthermore, we may expect high rates of loss to follow-up among both treated and untreated participants, as demonstrated by a recently published study from a similar setting [27]. 

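### Counting every missing outcome as an event bounds each model's absolute risk, but it is not a worst case for the comparison between models

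*Protocol article*

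**What the plan says.** The primary analysis (protocol article, Statistical analysis) is an adjusted Cox model for death or liver decompensation. People lost to follow-up are censored when last known to be alive. The same section then names a sensitivity analysis "assuming that all individuals with missing outcome data at the end of the observation period reached the primary outcome (worst case scenario"). It makes no distinction between models and gives no event time for the imputed events.

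The scale of the missing data has to be read from other places:

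- **Sample size and duration of the study:** "We anticipate that 5% of all included patients (treated and untreated) will either die or experience liver decompensation within 3 years" under the standard model, and "we want to detect a 50% relative reduction (Odds Ratio of 0.5 or less) with the test-and-treat model". After 997 per arm: "We will increase the sample size by 50% and aim for 1,500 patients per model of care arm, due to expected attrition".
- **Discussion:** "we may expect high rates of loss to follow-up among both treated and untreated participants". No figure is given.
- **Outcomes:** retention in care is a secondary endpoint in its own right. Health extension workers trace people who have missed appointments for over three months, and verify deaths. Decompensation is detected clinically.
- **Oversight, monitoring and dissemination:** a data analysis plan is still to be prepared.

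**The concern.** The primary analysis relies on censoring being unrelated to outcome, and the authors expect heavy loss. The sensitivity analysis therefore has to show whether informative loss could overturn the comparison between models.

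Adding an event for every missing person, in every model, does not show this. The events of interest are rare (2.5% to 5%), while the missing share may be several times larger. The recalculated event rate is then mostly a missingness rate, and the comparison mostly compares retention. If loss is similar in all models, a real benefit is diluted towards no difference. If loss differs, the model that keeps contact with more people looks safer whatever happened to patients. The results are meant to inform policy on who should be treated, so a check that could seem to refute a real benefit or support a false one matters.

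**Working it through.** **Inputs.** Three-year risks of 5% (standard) and 2.5% (test-and-treat), 997 evaluable per arm and 1,500 enrolled per arm come from the sample-size section. So does the design requirement, "with 80% power and 5% risk of type I error"; a two-sided test is assumed because sidedness is not stated.

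**Reproducing the plan's figure.** Two-proportion comparison, 5% vs 2.5%:

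n = [1.96 × √(2 × 0.0375 × 0.9625) + 0.842 × √(0.05 × 0.95 + 0.025 × 0.975)]² / 0.025² ≈ 906 per arm, or 984 with continuity correction.

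The stated 997 is within 3% of 984. Reading the effect as an odds ratio of 0.5 (2.56%) gives 962 or 1,043, neither within 3%.

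**Implied attrition.** 1 − 997/1,500 = 33.5%. This is an inference, so a range is shown below.

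**Equal loss, true halving.** With missing share d and risk p among those observed, the rate after imputation is d + (1 − d)p, and the imputed share of events is d / [d + (1 − d)p]. At d = 0.335:

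- Standard: 0.335 + 0.665 × 0.05 = 36.8%, about 552 events in 1,500; imputed share 0.335/0.368 = 91%.
- Test-and-treat: 0.335 + 0.665 × 0.025 = 35.2%, about 527 events; imputed share 0.335/0.352 = 95%.
- Risk ratio 0.955, against a true 0.50.

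Power is from a two-sided two-proportion normal test with 1,500 per arm:

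| Missing, both arms | Standard | Test-and-treat | Risk ratio | Imputed share of events | Power |
|---|---|---|---|---|---|
| 5% | 9.75% | 7.38% | 0.76 | 51% / 68% | 64% |
| 10% | 14.5% | 12.25% | 0.85 | 69% / 82% | 44% |
| 20% | 24.0% | 22.0% | 0.92 | 83% / 91% | 26% |
| 33.5% | 36.8% | 35.2% | 0.955 | 91% / 95% | 16% |
| 50% | 52.5% | 51.25% | 0.98 | 95% / 98% | 10% |

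Using 2.56% instead of 2.5% changes little: at 33.5% missing, the ratio is 0.956 and power 15%.

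**Unequal loss (the gaps are assumptions; the article gives none).**

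- No true effect (5% in both), 33.5% missing in standard and 28.5% in test-and-treat: 36.8% vs 0.285 + 0.715 × 0.05 = 32.1%. The odds ratio is 0.81, significant with probability about 78%.
- No true effect, gap reversed (31% in standard, 36% in test-and-treat): odds ratio 1.23, significant with probability about 77%.
- Extra loss that cancels a true halving: solve d + (1 − d) × 0.025 = 0.36825, so d = 0.34325/0.975 = 35.2%. That is 1.7 points above 33.5%. From a base of 10% missing, the gap is 2.3 points.

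**Is it a worst case for the contrast?** At 33.5% missing, the extreme against test-and-treat counts its missing as events and the standard model's missing as non-events: 35.2% vs 0.665 × 0.05 = 3.3%. The planned analysis gives 35.2% vs 36.8%, far from that bound.

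**What a tipping point would show.** Keep the standard model at 5% and let missing test-and-treat participants carry k times their model's risk: 0.025 × (0.665 + 0.335k). The ratio is 0.67 at k = 2, 0.84 at k = 3 and 1.00 at k = 4. The planned effect disappears at about a four-fold risk. This applies k to the whole three-year risk, so it is only a rough guide to a factor on the hazard after censoring.

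**The case against.** Several points on the other side stand.

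- **Worst case is a fair label for absolute risk.** The analysis gives an upper limit on each model's event risk, so it would be wrong to say that it carries no information.
- **The 33.5% is not a stated rate of missing outcomes.** It is the attrition that the inflation can absorb. Tracing will recover some outcomes, so the missing share could be lower. The table shows that this softens the problem without removing it.
- **The calculation is a binary approximation.** It ignores the six sites, covariate adjustment and time. The Cox version also depends on the event time given to imputed events, which the article does not state.
- **This is a secondary check.** The primary estimate, sample size and data collection do not depend on it.

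Three stronger readings are tempting, and the article does not support them. A reader might infer that no other sensitivity analysis will be done; it is the only one named, but a data analysis plan is pending and may add others. A reader might infer that retention is expected to differ between models. The article lists retention as an endpoint and expects high loss in treated and untreated alike, but predicts no difference. Visit schedules in Table 1 differ by treatment status, which makes a difference plausible and no more. Finally, a reader might infer that the check must contradict a true effect or confirm a false one; with equal loss it dilutes the ratio without reversing it.

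**Conclusion.** The point holds as a criticism of a method that the article fixes, not of something left out. The named analysis bounds each model's absolute risk but does not bound the comparison between models.

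The loss of information is large at the attrition implied by the plan's own inflation, and still material at a tenth or a twentieth missing. Imputed events are the majority in both arms throughout the range examined. The equal-loss results assume the planned 5% vs 2.5% among those observed. The results under unequal loss illustrate sensitivity to gaps that are assumed here; they do not forecast what this study will see.

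**What to change.** Make a model-specific tipping-point analysis the sensitivity check for the contrast. Impute event times for lost participants by multiple imputation, multiplying their hazard after censoring by a factor (for example 1, 2, 5 and 10) varied separately in each model. Report the combinations at which the conclusion changes.

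Use the vital status found by tracing to judge which factors are plausible for the death component. Tracing as described does not establish decompensation, so it cannot anchor that part of the composite.

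The all-missing-as-event analysis may stay as an upper bound on each model's absolute risk. The text should say that it is not a worst case for the comparison.

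The cost is a change of wording and modest extra programming, with no new data. It can go into the data analysis plan that is still to be prepared.

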### Oversight, monitoring and dissemination

A compact project management group will organize the training and oversee the implementation of the study. The project management group will visit the study sites at regular intervals throughout the study period to monitor progression, data quality, and confidentiality. A data monitoring committee has not been considered necessary. TDF has a very favorable safety profile. However, spontaneously reported adverse events will be recorded and assessed by the study management team. Additionally, individuals at risk of renal disease (age>60 years, diabetes mellitus, hypertension) will be subjected to regular monitoring of renal function (s-creatinine). There is no interim analysis planned, and no stopping procedure prepared. This is an observational trial and no external audits are planned. However, internal audits by the study management team will be performed at each study site at least annually. A data analysis plan and plan for dissemination will be prepared before data extraction has been completed. Results will be communicated to participants, stakeholders, and healthcare professionals. Abstracts will be submitted to scientific conferences and results published in peer-reviewed scientific journals.

Authorship will be determined according to the ICMJE authorship criteria. Contributors who meet all four criteria will be listed as authors on resulting publications. No professional medical writers will be used.

## Discussion

Here, we provide the structure and details of a prospective, multicenter cohort study assessing decentralized hepatitis B care in Ethiopia, aiming to compare three distinct models of care. We will assess clinical and programmatic outcomes over a 3-year period, and utilize methods from implementation science to assess the context where CHB treatment and care will be implemented. The study may have implications for patients with CHB as well as national and international health authorities and stakeholders, as the number of deaths due to CHB in the WHO Africa region is increasing and countries in the same region are struggling to make progress in their hepatitis B elimination efforts [1]. If one of the models is found to be superior and more and feasible to implement, it could be considered for broader implementation in other countries in the region.

One strength of the study is the utilization of existing health infrastructure, as we believe this increases sustainability and transferability of the study results. Besides training of staff, the study will utilize existing health structures and staff employed at local clinics/hospitals, to strengthen regional health authorities and ensure local support. Generalizability is increased by having two sites from separate regions of Ethiopia in every treatment model, and by taking a«real-world» pragmatic approach by having broad inclusion criteria and limited exclusion criteria. Key challenges will be to ensure that the six sites are able to complete the necessary screening efforts and reach the predefined sample size. Furthermore, we may expect high rates of loss to follow-up among both treated and untreated participants, as demonstrated by a recently published study from a similar setting [27]. 

A limitation of the study is the observational design. A cluster randomized trial would have ensured comparability of baseline characteristics across the three models, but was not possible with the available budget. Another limitation is the limited granularity in the assessment of deaths, as it is hard to distinguish liver-related deaths from non-liver related deaths in our setting. Lastly, a longer observation time would be preferable to demonstrate differences between the three models in terms of preventing liver failure or death, as liver related complications such as cirrhosis and HCC take time to develop. However, we argue that the effect of TDF on reducing the risk of liver failure or death can be measured within the designated observation period, as outlined in the sample size calculation [20, 28].

In conclusion, this observational cohort study will assess three models of decentralized care for delivering hepatitis B care in rural Ethiopia. From a public health perspective, identifying a simple, feasible and effective model of decentralized CHB care would be a key step to reduce liver-related mortality on the African continent. This study may have important policy implications and is expected to inform national and international hepatitis B elimination efforts in LMICs.

## Data Availability

No datasets are included in this manuscript, but the study protocol and data required to support the study protocol will be supplied on request.

## Abbreviations

ALT: Alanine aminotransferase
ANC: Antenatal care
AST: Aspartate aminotransferase
APRI: Aspartate aminotransferase to platelets ratio
CFIR: Consolidated framework for implementation research
CHB: Chronic hepatitis B
CICI: Context and implementation of complex interventions
CT: Computer tomography
DBS: Dried blood spot
HBV: Hepatitis B virus
HbsAg: Hepatitis B virus surface antigen
HBV DNA: Hepatitis B virus deoxyribonucleic acid
HCC: Hepatocellular carcinoma
HCV: Hepatitis C virus
HIV: Human immunodeficiency virus
LMIC: Low- and middle income country
LSM: Liver stiffness measurement
MRI: Magnetic resonance imaging
NA: Nucleos(t)ide analogue
SD: Standard deviation
TDF: Tenofovir disoproxil fumarate
WHO: World health organization
